## Abstract

**Background:**

Short-term and mid-term comparison of the efficacy of a multimodal program that incorporates a therapeutic workout program, medication review, diet adjustment and health education, in comparison to the standard medical practice in the improvement of the neuromuscular and physiological condition. Furthermore, it is intended to analyse the maintenance of these effects in a long-term follow-up (12 months) from the onset of the intervention.

**Methods:**

A randomized clinical trial of elderly frail patients drawn from the Clinical Management Unit “Tiro de Pichón”, Health District of Malaga, will be included in the study (after meeting the inclusion / exclusion criteria) will be randomized in two groups: a control group that will undergo an intervention consistent of medication review + diet adjustment + health education (regular workout recommendations within a complete advice on healthy lifestyles) and an experimental group whose intervention will consist of a multimodal treatment: therapeutic workout program+ medication review+ diet adjustment + health education. The sociodemographic, clinical and tracing variables will be reflected at the beginning of the study. In addition, the follow-up variables will be gathered at the second and sixth months after the beginning of the treatment and at the third and sixth months after the treatment (follow-up). The follow-up variables that will be measured are: body mass index, general health condition, fatigue, frailty, motor control, attention- concentration- memory, motor memory, spatial orientation, grip strength, balance (static, semi-dynamic), gait speed and metabolomics.

A descriptive analysis of the sociodemographic variables of the participants will be conducted. One-Factor ANOVA will be used for the Within-Subject analysis and as for the Between-Subject analysis, the outcome variables between both the groups in each moment of the data collection will be compared.

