## Methods/design

### Hypothesis

The interaction of various intervention strategies, wherein a supervised workout program, medication review, diet adjustment and health education are included, should achieve further improvements of the neuromuscular and physiological state in the elderly identified as frail, than the standard medical practice.

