### Sample size

To achieve a 80% statistical power to detect differences in the statistical hypothesis testing of the null hypothesis H through a bilateral chi-square test for two independent samples, considering that the significance level is 5%, and based on the studies contained in the Consensus Document on Prevention of Frailty and Falls in the Elderly by the Inter-Territorial Council 2014, a priori it is calculated, based on the outcome variable INTERFRAILTY Q included in one of the trials of such literature, by two means and adding a 15% of the losses (it will be necessary to include 100 subjects in the control group- standard medical practice- and 100 subjects in the experimental group – multimodal intervention program) amounting 200 subjects in the study.

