### Statistical analysis

A descriptive analysis of the socio-demographic variables of the participants will be conducted.

In order to analyse the existent differences in the variable values of interest between the control group and the experimental group, Student’s T-Test will be applied for two independent samples in the case that the normality condition could be accepted, which will be verified by the Saphiro-Wilk test. In case if normality couldn’t be accepted, the appropriate nonparametric test of Mann-Whitey will be conducted.

To analyse the existent differences in the response variables prior to and after the intervention, Student’s T-Test will be carried out for paired samples in the case that the condition of normality could be accepted. In any other case, the appropriate nonparametric test of Wilcoxon will be conducted.

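### Twelve outcomes are compared between groups at every visit, the only stated level is 5%, and no outcome or visit is named as the deciding one

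*Protocol article*

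**What the plan says.** - **Outcomes.** The Abstract (Methods) lists "body mass index, general health condition, fatigue, frailty, motor control, attention- concentration- memory, motor memory, spatial orientation, grip strength, balance (static, semi-dynamic), gait speed". With metabolomics, which it adds last, that makes 12 follow-up variables, the same 12 as in Table 1.
- **Visits.** The Abstract and the Experimental group section agree on four post-baseline measurements, at 2, 6, 9 and 12 months from the start of the intervention.
- **Between-group rule.** The Abstract says "the outcome variables between both the groups in each moment of the data collection will be compared". The Statistical analysis section applies a two-sample t-test, or Mann-Whitney if normality fails, "In order to analyse the existent differences in the variable values of interest between the control group and the experimental group". It does not narrow the set to one variable or one visit.
- **Error rate.** The only level is in Sample size: "considering that the significance level is 5%, and based on the studies contained in the Consensus Document". That section sizes the trial on the Inter-Frailty questionnaire. It does not call it primary and gives it no visit.
- **Hypothesis.** The multimodal program "should achieve further improvements of the neuromuscular and physiological state in the elderly identified as frail" compared with standard practice. No single measure is tied to that statement.

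**The concern.** The trial is sized for one test at 5%, but the analysis rule describes many tests at that level with none ranked above the others. The hypothesis is broad enough that grip strength, gait speed, balance or a metabolic marker could each be put forward as its confirmation. The variable behind the sample size is a self-administered survey of ten yes/no questions for detecting frailty (Inter-frailty section). It has no special standing in the analysis and is not a direct measure of the neuromuscular state named in the hypothesis.

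Two things are at stake. The 5% error rate used for sizing does not carry over to the conclusion of the trial, and the outcome and visit that decide success can be chosen after the data are seen.

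**Working it through.** **Inputs from the protocol article**
- 12 follow-up outcomes (Abstract; Table 1).
- 4 post-baseline visits (Abstract; Experimental group). Baseline is not counted.
- Level 5% (Sample size: "considering that the significance level is 5"), two-sided (Sample size: "through a bilateral chi-square test for two independent samples").
- 100 per group including 15% losses, 80% power (Sample size).

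**The plan's own figure.** The 200 subjects cannot be reproduced, because no effect size, SD or event rates are given. The number evaluable is 100 × (1 − 0.15) = 85 per group. At 80% power and two-sided 5%, that corresponds to a standardised difference of (1.96 + 0.84) × √(2/85) ≈ 0.43. This value is back-solved and is not stated in the document.

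**Number of tests.** 12 × 4 = 48. This is a minimum: SF-12 has a physical and a mental component, metabolomics covers at least three domains in Table 1, and the within-group before-after tests are left out.

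**Expected false positives under no effect.** 48 × 0.05 = 2.4.

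**If the tests were independent**
- Any significant difference, 48 tests: 1 − 0.95^48 = 91.5%.
- Favouring the program, 48 tests: 1 − 0.975^48 = 70.3%.
- Any significant difference, months 2 and 6 only (12 × 2 = 24 tests): 1 − 0.95^24 = 70.8%.
- Favouring the program, 24 tests: 1 − 0.975^24 = 45.5%.

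**With correlation.** The document gives no correlations, so these are assumptions. Test statistics were simulated as multivariate normal under no effect, with a common correlation between outcomes and another between visits. All outcomes were oriented so that higher favours the program.

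| Between outcomes / between visits | 48 tests, either direction | 48 tests, favouring program | 24 tests, favouring program |
|---|---|---|---|
| 0.2 / 0.6 | 82% | 50% | 35% |
| 0.3 / 0.5 | 81% | 48% | 33% |
| 0.3 / 0.7 | 75% | 42% | 31% |
| 0.5 / 0.7 | 65% | 34% | 24% |

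The comparator for a single two-sided 5% test is 5% in either direction and 2.5% favouring the program.

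**Inter-Frailty alone, unadjusted at four visits.** If independent, 1 − 0.95^4 = 18.5% in either direction. With between-visit correlation 0.5 to 0.8 it is about 16% down to 11%.

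**Why not simply adjust for 48 tests.** Bonferroni needs p < 0.05/48 = 0.00104, a critical value of about 3.28. At the back-solved 0.43 SD with 85 per group, the expected statistic is 0.43 × √(85/2) ≈ 2.80. Power is then 1 − Φ(3.28 − 2.80) ≈ 32%, against the planned 80%.

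**The case against.** **Multiplicity detail may sit elsewhere.** An article condenses, and adjustment methods and testing order are commonly left to an analysis plan, which is not shown. That stands for the finer detail. But the article states a rule that covers all the outcome variables at each collection point, and it is that rule which is challenged. The deciding outcome and visit are also design choices on which the sample size depends.

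**The rule is one Abstract sentence.** The Statistical analysis section speaks only of variables of interest. This is fair, but that section does not say which variables or visits those are, so it does not narrow the rule.

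**The Objective separates the visits.** It sets the efficacy comparison at short and mid term and uses the 12-month follow-up to look at maintenance. On that reading efficacy rests on months 2 and 6, or 24 tests. This is a reasonable reading, and its figures are given above; they are lower but still far above 2.5%.

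**Inter-Frailty is the natural primary outcome.** It is, since the trial is sized on it. It is still not designated and has no visit, and at four unadjusted visits its error would be about 11-19%.

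**Stronger readings.** A reader might infer that a false finding of efficacy is more likely than not. The numbers do not support that: the figures above 50% under correlation count differences in either direction, including those favouring control. Only independence takes the favourable-direction figure clearly past 50%, and that is implausible for repeated measures on the same people. A reader might also infer that any one significant test would be taken as confirming the hypothesis. No such rule is written; the Hypothesis and Discussion simply give no criterion for accepting it.

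**Conclusion.** The point holds. As written, the plan compares 12 outcomes at four visits, with 5% the only stated level and no deciding test, so the error rate used for sizing is not the error rate of the conclusion. The inflation is large on every reading examined. For a false result favouring the program, the chance is about 34-50% over 48 tests or about 24-35% over 24 tests, against 2.5% for a single test; if independent, the figures are 70% and 46%. These figures assume no true effect, correlations of 0.2-0.5 between outcomes and 0.5-0.7 between visits, and that a single significant result could be presented as success. The correlations are assumptions. The counts of outcomes and visits, and the absence of a designated comparison, come directly from the document.

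**What to change.** Before any data are reviewed, add one paragraph to the protocol, and update the registry record to match:

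1. Primary: the between-group difference in Inter-Frailty score at 6 months (end of intervention, on the variable used for sizing), tested once at two-sided 5%.
2. Key secondary, tested only if the primary is significant: one neuromuscular measure from Table 1 at 6 months, for example gait speed, also at two-sided 5%. This gives the stated hypothesis a matching test.
3. All other outcomes and visits: secondary, with 95% confidence intervals and no confirmatory claim.

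This needs no larger sample. It has two costs. Isolated significant results on other outcomes or visits become supportive only. And because Inter-Frailty comes first, a miss on it means that no formal claim can be made on the neuromuscular measure, even though that measure is closer to the hypothesis. The sponsor should accept that order knowingly.

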There will be three moments of data collection throughout the intervention: before the intervention, 2 months after the onset and after 6 months. Moreover, there will be a follow-up with two additional measurements: one 3 months and another one 6 months, after the conclusion of the intervention (9 and 12 months from the onset of the intervention, respectively).

The medication review will be focused on the regular, or at least every six months, review of the polypharmacy (intake of more than 5 drugs) insisting on the psychotropic medication due to its greater association to falls and the drugs that can negatively affect people with risk of falling under the STOPP/STAR criteria.

Diet adjustment includes the examination of the variety of nutrients and the protein intake as a protective factor. Anthropometric measurements, weight/height and BMI will be used.

The intervention on the potential hazards at home include conducting the home risk assessment template provided as the Annex 8 of the Consensus document on prevention of frailty and falls in the elderly, and intervening on modifiable elements, obstacles on the floor, mats, cables, lighting type at home, arrangement of the kitchen utensils, bathroom features, type of footwear, clothing and presence of pets.

Team members will reinforce the standard practice by the elements described above in order to improve the condition of frailty.

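### The between-arm test compares raw values at each visit and ignores the baseline already measured, which costs precision and lets chance imbalance into the estimate

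*Protocol article*

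**What the plan says.** The Hypothesis section of the protocol article is about comparative improvement: the multimodal strategy "should achieve further improvements of the neuromuscular and physiological state in the elderly identified as frail, than the standard medical practice".

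On timing, the Experimental group section states: "There will be three moments of data collection throughout the intervention: before the intervention, 2 months after the onset and after 6 months". Two further measurements follow at 9 and 12 months from onset. The Control group section gives both arms the same collection schedule.

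For the between-arm comparison, the abstract's Methods paragraph says that "the outcome variables between both the groups in each moment of the data collection will be compared". The Statistical analysis section names the test: Student's t-test "will be applied for two independent samples in the case that the normality condition could be accepted", with Mann-Whitney otherwise.

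The baseline value is used in only two other places: the one-factor within-subject ANOVA in the abstract, and the paired t-test or Wilcoxon test in the Statistical analysis section. No baseline covariate, between-arm contrast of change or group-by-time term is mentioned.

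**The concern.** The question is whether one arm improves more than the other. The stated between-arm test does not use the starting point, and the stated tests that do use it do not compare the arms. Significance in one arm and not in the other would not show that the arms differ.

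Two consequences follow for outcomes such as grip strength, BMI, gait speed and cognitive scores, where a person's later value can be expected to track the earlier one:

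- Stable differences between people stay in the error term, so the confidence interval is wider than it needs to be.
- A chance difference between the arms at baseline carries over into the follow-up difference and is read as part of the effect.

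In addition, a comparison at every collection point includes the one before the intervention. After randomisation any difference there is chance, so that test tells the reader nothing.

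This is separate from losses, multiplicity and the within-arm tests. It would remain with complete data, one outcome and one visit.

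**Working it through.** **Inputs from the Sample size section.** Power: "To achieve a 80% statistical power to detect differences". Level: "considering that the significance level is 5"%, two-sided. Size: 100 per arm, including 15% for losses. Evaluable per arm: 100 × (1 − 0.15) = 85.

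**The plan's own figure.** The 100 per arm cannot be reproduced. The section gives no effect size, SD or proportions. It says only that the figure is "based on the outcome variable INTERFRAILTY Q included in one of the trials of such literature", and it names a test of proportions ("through a bilateral chi-square test for two independent samples") while describing a calculation from two means. Read as two means, it can be solved backwards:

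d = (1.960 + 0.842) × √(2/85) = 0.43 SD

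The exact t-test gives 0.432. Going forwards, d = 0.43 needs 85 per arm, and 85/0.85 = 100. So 0.43 SD is the effect implied on that reading.

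**Assumed input.** The correlation r between baseline and follow-up is not in the document. It is taken as 0.3 to 0.9. The top of that range would suit only a very stable measure.

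**Gain from adjustment.** A linear model with baseline as covariate multiplies the residual SD by √(1 − r²). The detectable difference becomes 0.432 × √(1 − r²), and the equivalent raw sample size per arm is 85/(1 − r²).

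| r | √(1 − r²) | Detectable at 80% power (SD) | Power at 0.43 SD | Power at 0.30 SD | Raw n per arm for the same precision |
|---|---|---|---|---|---|
| raw test | 1 | 0.43 | 80% | 49% | 85 |
| 0.3 | 0.954 | 0.41 | 84% | 53% | 93 |
| 0.5 | 0.866 | 0.37 | 90% | 61% | 113 |
| 0.7 | 0.714 | 0.31 | 97.5% | 78% | 167 |
| 0.9 | 0.436 | 0.19 | above 99% | 99% | 447 |

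The 0.43 SD column uses the normal approximation and the 0.30 SD column the t-test. The 0.30 SD effect is an illustration and not a figure from the plan. A simulation (4,000 trials, 85 per arm, d = 0.43) gave 79.8% raw against 89.8% adjusted at r = 0.5, and 79.5% against 97.2% at r = 0.7.

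**Chance imbalance.** The standard error of the baseline difference, in SD units, is √(2/85) = 0.153. The chance that the arms differ by more than 0.2 SD on a given outcome is P(|Z| > 0.2/0.153) = 19%.

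The raw follow-up difference is shifted by r times the imbalance. At r = 0.7 and 0.2 SD the shift is 0.7 × 0.2 = 0.14 SD. With no true effect, the chance of significance in that direction is then

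P(N(0.14, 0.153 × √(1 − 0.49)) > 1.96 × 0.153) = 7.1%.

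With no imbalance the same formula gives 0.3%. Over all randomisations the figure is 2.5% per direction.

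**The case against.** The strongest reply is that the stated test is valid. In a randomised trial the unadjusted comparison is unbiased and keeps its 5% level overall. If the sample size was set from two means, it also has its planned 80% power at the implied 0.43 SD. This stands. The 7.1% is conditional on a particular imbalance and is offset by lower rates when the arms are well balanced. It is not an inflated overall error rate, and the trial is not underpowered against its own design on this account.

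The gain also depends on a correlation that the document does not give. The one outcome named for sizing is a questionnaire of 10 yes/no questions, and visits run to 12 months. At r = 0.3 the gain is only from 80% to 84%. This stands too: the upper rows of the table should not be assumed for every outcome. The direction holds for any correlation that is not trivial.

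A third reply is that the Statistical analysis section speaks of variable values without saying levels or changes, and that covariates are often left to an analysis plan. This does not carry far. The article names its tests in two places, and the abstract's wording points to levels at each visit. If change scores were meant, the text still needs correcting, and they would be a poorer choice: at 0.43 SD their power is 66%, 80% and 95% at r = 0.3, 0.5 and 0.7, below adjustment each time and below the raw test at 0.3.

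**Conclusion.** The concern holds. As written, no between-arm analysis uses the baseline value, although the hypothesis concerns improvement and the value is collected in both arms.

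The cost is lost precision and exposure to chance imbalance, not an invalid test. With 85 evaluable per arm, adjustment would lower the detectable difference from 0.43 SD to 0.41, 0.37 or 0.31 SD at r = 0.3, 0.5 or 0.7. It would also remove the carried-over imbalance, which is 0.14 SD for a 0.2 SD baseline difference at r = 0.7. These sizes rest on the assumed correlations, on a 15% loss and on approximately normal outcomes.

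The sponsor should make the change. The control arm also receives medication review, a diet plan and exercise advice, so the contrast rests largely on the supervised training and the added effect may be modest.

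**What to change.** In the Statistical analysis section and the abstract's Methods paragraph:

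1. Replace the raw between-arm test at each post-baseline visit by a linear model of the visit value on arm and the same variable's baseline value. Report the adjusted mean difference with its 95% confidence interval. A repeated-measures model with baseline as covariate and an arm contrast at each visit serves equally well.
2. If age and sex are to be added (both are already collected), name them in advance so that the covariate set is not chosen after the data are seen.
3. Say what replaces the switch to Mann-Whitney for skewed or bounded scores, for example the same adjusted model with robust standard errors, or an adjusted analysis on ranks.
4. Drop the significance test between arms at the visit before the intervention and show baseline values descriptively by arm.

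The cost is a few sentences. No new data, visits or patients are needed.

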**Discussion:**

A multimodal program that incorporates a therapeutic workout program, medication review, diet adjustment and health education may be effective treatment to reduce the functional decline in elderly. The results of the study will provide information on the possible strengths and benefits in multimodal program in elderly.

**Trial registration:**

ClinicalTrials.gov NCT02772952 registered May 2017.

## Background

In the year 1990, the WHO defines the elderly population as people aged 65 or above [1]. In the recent years, a new paradigm of aging has emerged that has been addressed as: healthy, good aging, competent, successful or active [2]. This concept has evolved, back from the definition of healthy aging given by the WHO in 1990 (health centralized), towards a much more integrated model, such as the one of active aging [3]. Aging is a deleterious, progressive, intrinsic and universal process that eventually occurs in all living entities as a result of the interaction of a living being’s genetics and its environment [4]. The ways of aging are neither determined nor prefixed; and although we can’t ignore that there are genetic variables that play an important role in aging, the individual is also responsible for a, more or less, satisfactory and free from dependence aging, with its actions and behaviour throughout its life [2], hence making it possible to discuss three basic forms of aging: usual, pathological and optimal aging [2].

According to the recent estimations, the world population above 65 years old were 528 million in the year 2010, and will be more than 605 million in the year 2015. The United Nations forecast for Spain in the year 2015, for the population above 65 years, is estimated in more than 8 million of subjects [5], entailing more than 18% of the Spanish population (CNE, Centro Nacional de Epidemiología). The Ministry of Health and Consumer Affairs claims that life expectancy draws an ascendant progression in most of the developed countries; nevertheless, that doesn’t necessarily imply that the increased number of years in this indicator would be years in a good health condition. In most of the cases, the elderly population are affected by diseases and health issues that result in quality of life deterioration, even if they don’t occur in immediate death [6].

Aging has been traditionally treated as rather “pathological” [7]. Nonetheless, this vision is being replaced by another one that defends that, although there are certain diseases that indeed appear more frequently in the old age than in other stages of life, this doesn’t mean that both of these aspects are intrinsically associated [7]. In fact, there is enough empirical evidence to assert that both health care interventions and lifestyle habits significantly contribute to an improvement of a life expectancy without any impairments [7, 8].

Hence, there is a pressing need of identifying those factors that influence the onset of impairment and dependence in the elderly, both of which notably deplete the quality of life in this age group [7, 8]. It is in this context that the concept of “frailty” appears, a concept that refers to something that can relatively deteriorate with ease [7, 8]. Currently it’s defined as a biological syndrome with a decrease of the reserve and endurance to physical and psychological stress factors that increase the vulnerability to adverse situations [7]. This concept has gained importance since its inception and it has risen to take an important role in the scientific literature on aging. At present, frailty is assumed to be a construct that often underlies health deterioration that occurs in the elderly, there being an emerging agreement that the frailty markers include age related reduced lean body mass, strength, endurance, balance, walking speed and low activity [8].

Moreover, while frailty, impairment and dependence typically coexist, frailty seems to be prior and, thus, likely to be early intervened on [9]. Therefore, it’s crucial to specifically identify the features of the people that confirm the group of “elderly frail” being convinced that this information could help to elaborate targeted interventions to prevent and/or to a more effective intervention in the courses of impairment and dependence. It is here where the starting point of the current investigation work is established.

Frailty commonly has a major impact on the patient’s quality of life, leading to undesirable consequences in the physical capacities, intellectual activity, emotional aspects, personal relations and cognitive issues [10]. Among the most frequent cognitive problems, decreased selective attention, loss of memory, mental confusion, and concentration difficulties, are described [11]. Despite there being a great emphasis to the assessment of the cognitive problems, these shouldn’t be solely interpreted, as the consequences could have a negative reflection on the functional impairment, depressive states, sleep pattern variations, and even social vulnerability [12]. A reliable, inexpensive and valid way to identify the effect that the patient suffers is using self-administered surveys [13]. The results of patient-provided measures are used as an assessment and/or follow-up tool to objectively reflect the patient’s health condition or its functional status at a specific moment. These tools help the physicians to understand the impact of a disease or condition over the patient’s symptoms, performance and skills.

Furthermore, changes and modifications that occur as a result of frailty, are reflected in the body’s metabolic balance [14]. These changes can be collected and analysed through the use of metabolomics (a technique that comprises the development of systematic profiles from the multiple metabolite concentrations and their cellular and systemic fluctuations in response to drugs, diet, lifestyle, environment, stimuli and genetic modulations, in order to distinguish beneficial and adverse effects of such interactions [15]. By systematically measuring biomarkers (metabolites) in the population, profiles can be set among healthy individuals from those with specific diseases [16]. Moreover, metabolomics may provide signs of a metabolic disorder or a lesion with high precision and less cost than genomics, transcriptomics or proteomics [17].

Finally, the evaluation of the physical function is an important component of the geriatric assessment in the elderly [18, 19]. These measurements have shown to have sufficient discriminating sensitivity and have proven the ability to predict the outcomes, such as risk of falls, institutionalization, and death [20, 21]. There are tests based on the strength, walking speed or the transition between the different daily life positions that have proven to have a high sensitivity in the diagnosis of frailty [19, 21]. This set of tests to assess fitness and performance have proven to be reliable and valid for assessing the functional impairment in the elderly that live in nursing homes [20]. Recently, several studies have examined the functional physical function which make up the functional test and the instruments used, together with improvements to the instruments, specifically attaching inertial sensors to the body [22–44].

The specific applications for these elements are already being developed for use in a wide range of situations [44, 45]. Such uses include assessing and quantifying kinematic variables related to functional tasks [24–26, 43], identifying trembling in people suffering from Parkinson’s disease [22] and measuring Cobb angles in X-rays [45]. Another application is the development of an objective method to classify levels of physical activity and an indicator of the degree of functional capacity and quality of life [46] and gait characteristic analysis and identification based on the smartphone’s accelerometer and gyrometer [47].

Therefore, the use of different assessment methods by means of which the elderly are analysed from different perspectives (physical, mental, metabolomics, subjective, etc.), could help to identify the elderly frail, which would enable setting up the intervention protocols intended to reverse theses deficient states or at least, slowing their progression.

In this respect, in order to planning any intervention, it’s important to note that the quality of muscle mass, namely, force production per unit of active muscle mass, has been associated to the functional ability in the elderly population [48]. Muscle quality provides an estimate of the contribution of the neuromuscular factors related to changes in the development of strength, as when the strength is increased while maintaining the same muscle mass, this suggests neural adapting to training [49].

In this sense, a combination of strength and endurance training in the elderly population has been suggested to be the most effective strategy to improve both neuromuscular and cardiorespiratory functions, the preservation of the functional ability and health promotion during old age [50, 51]. However, several studies have proven that in the simultaneous training, the “interference effect” may appear, reducing the strength adaptations when it is compared to only strength training [52], even when the participants of the training protocols are the elderly, [50, 51], being noticed not only in the strength training, but as well in those that are intended to a better cardiorespiratory performance in the elderly population [50, 51]. Thus, along with the amount of aerobic training and intensity, within-session workout sequence could be an important variable in the prescription of simultaneous training [50], as the strength performance just before the endurance training compromises endurance gaining [50].

A decrease in muscle quality has been associated with decreased functional ability in the elderly population [48]. To counteract this process, some studies have proven that quality strength training increases muscle mass in the elderly [49–51].

